#### Recruitment

Inclusion criteria for patients are: (ii) being scheduled for primary or revision UKA or TKA by an orthopedic surgeon between January 2022 and July 2023; (ii) having paid work for at least eight hours a week before surgery; (iii) being between 18 and 65 years of age and (iv) having the intention to fully RTW after surgery. Criteria to exclude patients are: (i) receiving more than one medical event within one year that affects work ability after KA; (ii) having a KA for any other reason than knee osteoarthritis; and (iii) having major disabling mental disorders. Patients who do not speak or read Dutch are given the opportunity to fill in the questionnaires with the aid of a translator and to have an interpreter present during the consultations. Patients who are eligible to participate are informed about the study by telephone by the medical case manager (MCM; physical therapist working in the hospital). During an intake consultation with an MCM, the patient information letter, informed consent, and an infographic of the BAAS clinical pathway (Additional file 1: Appendix I) are handed out to the patient. Patients’ questions regarding participation are answered. Patients are given one week to decide whether or not they wish to participate. Patients who opted for the possibility to participate receive a telephone call after one week so that they can ask any additional questions about the study and they will be asked if they want to participate. Participants willing to participate sign the informed consent.

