**Table 1 Tab1:**
[figure not shown]
Measurements on different time points

T_0_ = baseline; T_1_ = 6 weeks after surgery; T_2_ = 3 months after surgery; T_3_ = 6 months after surgery; T_4_ = 9 months after surgery; T_5_ = 12 months after surgery

*Abbreviation*: *CSI* Central sensitization inventory, *DEMMI* De Morton mobility index, *FTST* Five time sit to stand test, *iPCQ*, *KOOS* Knee osteoarthritis outcome score, *WORQ* Work Osteoarthritis and joint-replacement questionnaire, *6 MWT* 6-Minute walk test, *30-STST* 30 Seconds sit to stand test. * = follow-up measurements stop after full return to work

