### Measures

#### Primary outcomes

For the study on effectiveness, the primary outcomes are first day of RTW and/or first day of full RTW. First day of RTW is defined as: time in days from surgery to the first day of returning to work, regardless of the number of working hours or tasks performed. Full RTW is defined as: time in days from surgery to the first day a patient works the number of hours stated in his or her employment contract regardless of the tasks performed. For self-employed patients, full RTW is defined as: the first day of the week a patient works the number of hours equal to the number of hours he or she worked before surgery. For the first days to RTW the prospective Expect to Work study by Van Zaanen et al. will be used as usual care cohort, and for full RTW the ACTIVE trial comparison group by Straat et al. will be used [17, 18]. Test–retest reliability, minimal clinical importance difference, and minimal detectable difference of self-reported RTW are not described in the medical literature, if we are not mistaken. The effectiveness study of BAAS will be reported according to the Strengthening the Reporting of Observational Studies in Epidemiology (STROBE) guidelines [19].

For the economic evaluation, the primary outcomes are the total costs of the intervention, and the societal and health care cost obtained by a cost-questionnaire at 3, 6, 9 and 12 months according to the guidelines of the Dutch Health Care Institute (Zorginstituut Nederland), in line with the study performed by Straat et al. [17, 20]. The economic evaluation will be reported according to the Consolidated Health Economic Reporting Standards 2022 (CHEERS 2022) and we will use the human-capital method [21].

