#### Demographics

We will collect age, sex, length, weight, type of surgery (UKA/TKA), side of surgery (left/right), length of stay, working hours per week, working days per week, physical nature of the job, preoperative sick-leave days, breadwinner, being self-employed, comorbidities, and complications after surgery.

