During the hospitalization, the patient receives perioperative care as usual according to the KA fast track principles in both hospitals [42]. At NS hospital, patients who have decided to have KA receive an Oxford uncemented Partial Knee (Zimmer Biomet), NexGen LPS-Flex or CR Total KA (Zimmer Biomet) or Medial Rotation Knee total knee replacement (BdH Medical BV) or SAIPH Knee System (BdH Medical BV). At ETZ hospital, patients who have decided to have KA receive a SIGMA Total Knee System (Johnson and Johnson) or an Oxford Partial Knee (Zimmer Biomet).

In both hospitals, patients will receive physical therapy according to usual care while being hospitalized for two or three times a day, with the goal of gaining independence in activities of daily living such as walking, transfers in and out of bed or chair, and walking up and down stairs if necessary [43]. Also, the orthopedic surgeon and physical therapist motivate the patient to train range of motion of the knee to at least full extension (0 degrees) and 90 degrees of flexion. After hospitalization, the patient receives physical therapy from a primary physical therapy setting according to the patient’s preferences and taking into account the Royal Dutch Society for Physiotherapy (KNGF) guidelines for knee osteoarthritis [44]. The physical therapist is informed that the patient is participating in BAAS care pathway, and informed about the content of this pathway through an information letter. A work-related therapy goal is set up from the start of the therapy and monitored every six weeks throughout the whole clinical care pathway using Goal Attainment Scaling (GAS, Fig. 1) by the MCM. Progress in recovery is evaluated through questionnaires (WORQ, KOOS, and CSI), functional capacity test (floor-to-waist lifting test), functional tests (DEMMI, FTST, and 6MWT) and the physical activity level measured by the accelerometer (Table 1). The questionnaires and functional capacity evaluations tests are repeated at 6 weeks and every 3 months after surgery (Fig. 1), with the exception of the floor-to-waist lifting test at six weeks after surgery due to patient safety reasons. Data from the accelerometer is evaluated by the MCM on a weekly basis. Stop criteria for the BAAS clinical pathway are full RTW or, if RTW was not achieved after one year.

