In transition processes, in which care as usual is replaced by a new care pathway, the essential role of the patients and health care professionals is often overlooked. Therefore, in our study the professionals involved in the care transitions in the two hospitals will collect and scrutinize the data together and, based on the results, determine what kind of action should be performed to enhance RTW in close contact with the patient. One of the consequences of this iterative cycle will be that all professionals as well as the patients involved become partners in achieving an optimal RTW. This way, the embedded scientist who, in daily practice, collects, creates, and reviews knowledge, and investigates the effectiveness of this newly implemented care pathway is an essential actor in creating and implementing future RTW pathways for other groups of working age patients.

Lastly, by using the data from two Dutch cohorts on RTW with similar inclusion criteria, our study is designed to be more cost-effective than a randomized controlled trial.

The limitations of this study protocol are that the lead author has an active role as an MCM in this study. This is why we included patients from a second hospital (ETZ). Also, we will not perform an RCT. We will use the data from two other prospective cohort studies with similar inclusion criteria to compare our findings to usual care. The care for knee arthroplasty is, fortunately, largely standardized in the Netherlands [44, 53]. Also, we will use propensity analysis to reduce the bias due to possible differences between our cohorts and the two comparison cohorts [17, 18].

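### Exclusion criterion (i) is not tied to enrolment and can be read as excluding patients for medical events inside the 12-month outcome window

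*Protocol article*

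**What the plan says.** The Recruitment section of the protocol article lists three exclusions. The second (an indication other than osteoarthritis) and the third (major disabling mental disorder) can be checked at intake. The first excludes patients "receiving more than one medical event within one year that affects work ability after KA". It gives no start for the year, does not separate planned from unforeseen events, and does not say who judges them or when.

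The same section places eligibility before surgery: "Patients who are eligible to participate are informed about the study by telephone by the medical case manager". Intake, a week for reflection and consent follow.

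Under Primary outcomes, first RTW is "time in days from surgery to the first day of returning to work, regardless of the number of working hours or tasks performed"; full RTW also runs from surgery. The last measurement in Table 1 is "T_5_ = 12 months after surgery".

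Three other places bear on the reading:
- Study intervention: "Stop criteria for the BAAS clinical pathway are full RTW or, if RTW was not achieved after one year". Medical events are not named as a reason to stop.
- Demographics: the data to be collected include "comorbidities, and complications after surgery".
- Discussion: "We will use the data from two other prospective cohort studies with similar inclusion criteria to compare our findings to usual care". The article does not say whether criterion (i) holds in those cohorts.

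**The concern.** An eligibility rule should depend only on what is known when the patient enters. This one refers to events within a year and to work ability after the operation, without limiting the events to those already known. On its literal reading it can be settled only during follow-up, and an event that affects work ability is by its nature a cause of late RTW. Excluding on such events would be selecting on the course of the outcome.

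The design makes this matter. BAAS is a single cohort compared with individual data from two external usual-care cohorts, so any selection applied on one side only goes straight into the contrast. The economic evaluation uses the same BAAS patients (Patient timeline), so absenteeism and health care costs would shift in the same direction. The medical case manager both informs eligible patients (Recruitment) and collects the RTW data (Data collection), so an undated criterion leaves room for judgement by someone who may know the outcome.

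**Working it through.** **Reading the text.** The plan gives no figure on this point, so there is none to reproduce. Side by side:

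1. Eligibility is settled before surgery (Recruitment).
2. Time zero is surgery (Primary outcomes) and follow-up ends at 12 months (Table 1).
3. If the year in criterion (i) starts at surgery, it coincides with the outcome window, and unplanned events in it are unknown at step 1.
4. The matching variables (Statistical methods, Effectiveness) are UKA or TKA, gender, BMI, physical nature of the job, preoperative sick leave and work-relatedness of symptoms. The mixed model adds primary versus revision surgery. All are preoperative or surgical, so neither matching nor adjustment can undo a selection on later events.

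**Possible size.** Let *q* be the share of the BAAS cohort removed and *D* the number of weeks by which their mean RTW exceeds that of the patients retained (mean *m*). The full-cohort mean is (1 − q)·m + q·(m + D) = m + q·D. Removal therefore shortens the observed mean by **q × D**. Both *q* and *D* are assumptions; the documents give neither. The relevance thresholds come from Statistical methods: two weeks for first RTW and one week for full RTW.

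| q (of 150 planned) | D = 4 weeks | D = 13 weeks | D = 26 weeks | D needed for 1 week (1/q) | D needed for 2 weeks (2/q) |
|---|---|---|---|---|---|
| 2% (3 patients) | 0.08 | 0.26 | 0.52 | 50 | 100 |
| 5% (7.5 patients) | 0.20 | 0.65 | 1.30 | 20 | 40 |
| 10% (15 patients) | 0.40 | 1.30 | 2.60 | 10 | 20 |

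The range is 0.08 to 2.60 weeks. At 2% removed, neither threshold is passed at any delay shown. At 5%, the one-week threshold is reached with a 20-week delay and the two-week threshold only with 40 weeks. At 10%, the delays needed are 10 and 20 weeks.

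For scale, the Discussion gives mean first RTW as 6.4 weeks in the feasibility study and 12.9 weeks in a comparison study. A delay of 26 weeks would put the removed patients at about 6.4 + 26 = 32.4 to 12.9 + 26 = 38.9 weeks. That is possible within a 12-month follow-up but at the high end.

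**The case against.** A reader might infer that the plan deletes slow returners from the BAAS cohort while leaving them in the controls. The documents do not support that:

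- No passage describes removal after enrolment. The criterion stands among recruitment criteria that are otherwise settled before surgery. The pathway's stop rule names only full RTW and one year, and the analysis sections plan imputation without any exclusion after enrolment.
- Collecting complications after surgery suggests that patients who have them stay in the data.
- A baseline reading fits the words: receiving more than one event suits planned procedures, such as a second operation already scheduled within the year, and the reference to KA may qualify work ability rather than date the events.
- The rule requires more than one event. Unless the arthroplasty itself counts, a patient with a single complication stays in, so the affected group may be small.
- Different handling of the controls is not shown. The article calls their inclusion criteria similar, and the source studies are not at hand.
- The size is illustrative, and it is a shift in a raw mean, whereas the plan also specifies survival analysis with hazard ratios.

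All of this stands, and it rules out presenting the deletion, or a bias of given size, as fact. It does not remove the ambiguity. The article states this criterion rather than leaving it to a fuller document, and following it literally would conflict with the stop rule. The baseline reading, too, calls for the same rule in the control data.

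**Conclusion.** The point holds as a defect of wording with a conditional risk of bias. Criterion (i) is not tied to enrolment and can be read as excluding patients for more than one work-affecting event in the year after surgery. Under the baseline reading, applied equally to the controls, there is no bias. If it were applied after surgery in BAAS only, the bias would favour BAAS on time to RTW and costs, and the planned matching would not correct it.

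The size cannot be computed from the documents. For assumed shares of 2% to 10% and delays of 4 to 26 weeks it runs from about 0.1 week, which is negligible, to 2.6 weeks. It passes the one-week threshold for full RTW only when share and delay are both fairly large, and the two-week threshold for first RTW only near the top of the range. The stronger conclusion, that BAAS results will be flattered by removing slow returners, needs two facts that the documents do not give: that removal after surgery takes place, and that the controls are treated differently. The change is still worth making, because it is cheap and closes a route to bias that the analysis cannot repair.

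**What to change.** 1. Reword criterion (i) so that it refers only to other medical events known or scheduled at enrolment that are expected to affect work ability within the year after surgery, and state that it is judged before surgery.
2. State that every enrolled and operated patient stays in the primary analysis whatever events occur later, for both effectiveness and costs.
3. Apply the same baseline criterion to the individual data of both control cohorts before matching, as far as those data allow, and report where they do not.
4. Check the screening log. If any patient was excluded for an event that arose after enrolment, include that patient in the primary analysis and report the analysis without such patients as a sensitivity analysis only.

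The cost is a one-sentence amendment, a log check and one filter on the control data. The downside is that observed RTW times in the BAAS cohort may be slightly longer.

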#### Patient timeline

Since the analysis on effectiveness and economic evaluation will be conducted on the same cohort, the participant timeline will be identical (Fig. 1 and Table 1).

**Fig. 1 Fig1:**
[figure not shown]
The BAAS clinical pathway. Abbreviations: 6MWT = 6-min walk test, CRT = Chair Rise Time, CSI: Central Sensitization Inventory, DEMMI = de Morton Mobility Index, FTST: Five Time Sit to Stand, iPCQ = iMTA Productivity Cost Questionnaire, KOOS = Knee Osteoarthritis Outcome Score, OP = occupational physician, RTW = RTW, WORQ = Work, Osteoarthritis and Joint-Replacement Questionnaire

**Table 1 Tab1:**
[figure not shown]
Measurements on different time points

T_0_ = baseline; T_1_ = 6 weeks after surgery; T_2_ = 3 months after surgery; T_3_ = 6 months after surgery; T_4_ = 9 months after surgery; T_5_ = 12 months after surgery

*Abbreviation*: *CSI* Central sensitization inventory, *DEMMI* De Morton mobility index, *FTST* Five time sit to stand test, *iPCQ*, *KOOS* Knee osteoarthritis outcome score, *WORQ* Work Osteoarthritis and joint-replacement questionnaire, *6 MWT* 6-Minute walk test, *30-STST* 30 Seconds sit to stand test. * = follow-up measurements stop after full return to work

### Measures

#### Primary outcomes

For the study on effectiveness, the primary outcomes are first day of RTW and/or first day of full RTW. First day of RTW is defined as: time in days from surgery to the first day of returning to work, regardless of the number of working hours or tasks performed. Full RTW is defined as: time in days from surgery to the first day a patient works the number of hours stated in his or her employment contract regardless of the tasks performed. For self-employed patients, full RTW is defined as: the first day of the week a patient works the number of hours equal to the number of hours he or she worked before surgery. For the first days to RTW the prospective Expect to Work study by Van Zaanen et al. will be used as usual care cohort, and for full RTW the ACTIVE trial comparison group by Straat et al. will be used [17, 18]. Test–retest reliability, minimal clinical importance difference, and minimal detectable difference of self-reported RTW are not described in the medical literature, if we are not mistaken. The effectiveness study of BAAS will be reported according to the Strengthening the Reporting of Observational Studies in Epidemiology (STROBE) guidelines [19].

For the economic evaluation, the primary outcomes are the total costs of the intervention, and the societal and health care cost obtained by a cost-questionnaire at 3, 6, 9 and 12 months according to the guidelines of the Dutch Health Care Institute (Zorginstituut Nederland), in line with the study performed by Straat et al. [17, 20]. The economic evaluation will be reported according to the Consolidated Health Economic Reporting Standards 2022 (CHEERS 2022) and we will use the human-capital method [21].

Costs of the BAAS care pathway intervention include: (i) cost of case managers; (ii) cost of compiling the report by the OCM; (iii) cost of professionals present at the digital interdisciplinary consultation and (iv) cost of the use of the accelerometer program. These costs will be estimated using the micro-costing approach. In other words, the cost estimation will be based on actual resources depleted, which will be assessed using prospective data collection, and will be valued in accordance with the Dutch guidelines for conducting economic evaluations in health care [20]. Societal cost includes occupational health care services, informal care, unpaid productivity loss, absenteeism, presenteeism and other health care services. Absenteeism (e.g. total number of sick leave days, measured prospectively by the MCM) and presenteeism (e.g. lower productivity as compared to normal while at work) will be valued using sex-specific price weights [20]. Unpaid productivity losses (e.g. voluntary work) and informal care are measured by asking the number of hours per week patients were unable to perform unpaid activities in the cost-questionnaire. Unpaid productivity losses and informal care will be valued using a recommended Dutch shadow price [20]. Using consumer price indices, all costs will be converted to the same reference year by using the human-capital method.

For health care costs, all costs according to the formal Dutch health care sector will be obtained, including cost of primary care (e.g. family physician or primary care physical therapist), secondary care (e.g. hospital stays and visits), tertiary care (vocational rehabilitation) and medication. If available, these will be valued using Dutch standard costs [20]. If unavailable, prices of professional health care organizations will be used. Medication use will be valued using prices derived from http://www.medicijnkosten.nl. All costs will be summed and divided by the number of participants, separate for both groups. This will lead to average (95% CI) total costs per participant.

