## Methods

### Study design

This protocol paper has been written in line with the standards of Standard Protocol Items: Recommendations for Interventional Trails (SPIRIT) [16]. We will perform a multicenter prospective cohort study with patients who have decided to be given a total KA (TKA) or a unicompartmental KA (UKA). To establish generalizability, the BAAS pathway will be performed in two high-volume KA hospitals in the Netherlands serving a representative population of working patients receiving KA. For the effectiveness of BAAS regarding RTW, the results of the study will be matched in pairs and compared to individual patient data on RTW by matched pairs from prospectively performed cohort studies in the Netherlands on care as usual, namely the Expect to Work cohort and the ACTIVE trial [17, 18]. For the economic evaluation, a comparison will be made with individual patient-level data using the care-as-usual group of the ACTIVE trial in the Netherlands [17]. The study has been approved by the Medical Ethical Committee of the Amsterdam UMC, location AMC (reference ID: W21_454 # 21.504) and the Medical Ethical Committees of the local hospitals Nij Smellinghe (NS, reference ID: 19,888) and Elizabeth Tweesteden Ziekenhuis (ETZ, reference ID: L1429.2021).

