### Participants

#### Sample size

A minimal required sample size was calculated using R (version 3.6.3) with a power of 0.8 and a significance level of 0.05. The effect size was calculated with a mean difference of two weeks in comparison to a Dutch study on RTW after KA [15]. With a calculated minimal required sample size of 125 and an expected loss to follow-up of 20%, we intend to include 150 patients (75 in NS and 75 in ETZ).

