### Statistical methods

#### Effectiveness

The effect of the BAAS care pathway on time to RTW will be statistically tested using survival analysis and gamma regression analysis including bootstrapping using R (version 4.1.0). Missing data will be handled by multivariate imputation using the aforementioned prognostic factors if possible [46]. For the repeated measurements on the time to RTW and/or full RTW, a mixed model will be used to test and estimate the size of the BAAS effect controlling for the following potential prognostic factors of delayed RTW, namely UKA vs TKA, primary vs revision KA, gender, BMI, physical nature of the job, preoperative sick leave, and patient-reported work-relatedness of knee symptoms. Hazard ratios including 95% confidence intervals will be calculated for the intervention group and tested against both control groups. In the absence of an empirically derived MCID, a difference of two weeks will be considered clinically relevant for first day of RTW and one week for full RTW. For interpreting the magnitude of the standard mean difference (SMD), three groups are defined: (i) small (SMD = 0 – 0.2); (ii) medium (SMD = 0.2 – 0.5) and (iii) large (SMD = 0.5–1.0) [47]. Sensitivity analyses on RTW will be performed for the two hospitals. Analyses will be conducted using both univariate and multivariate analyses to assess the effect size of the BAAS care pathway with and without controlling for variables. Lastly, because this control group is not from the same cohort as the intervention group, we will use propensity analysis (matched pairs) to correct for other confounding factors [48]. Potential prognostic factors for delayed RTW like UKA vs TKA gender, BMI, physical nature of the job, preoperative sick leave and patient-reported work-relatedness of knee symptoms will be used for patient matching. Secondary outcomes will be plotted in time and will be tested on differences between the usual care cohorts and the intervention cohort.

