## Discussion

This study describes the protocol to evaluate the effectiveness of the BAAS care pathway for RTW as well as its costs and benefits. To the best of our knowledge, this is the first work-directed and patient-centered care after KA systematically involving health care experts other than an orthopedic surgeon and a physical therapist.

To the best of our knowledge, there is no previous study concerning minimal clinical differences in return to work after surgery. Therefore, we held a consensus meeting with authors [name] in which we concluded that a minimal clinical difference of two weeks on start to return to work and one week for full return to work is relevant.

Until now, no core outcome set exists for work participation including RTW to be used in intervention studies [49, 50]. Previous studies on RTW among patients with knee arthroplasty defined RTW in different ways. For example, Hylkema et al. measured the proportion of full RTW within 3, 6 or 12 months by asking the patient via a questionnaire whether they partially or fully returned to work, or not at all [6]. Tilbury et al. measured RTW by asking patients through a follow-up questionnaire what the duration from operation until the first day of RTW was [15]. Systematic reviews on RTW among patients with knee arthroplasty concluded that pooling data on RTW results in heterogeneity due to these varying RTW outcomes. To obtain a valid comparison, we used the same RTW definitions as those used in the prospective studies of Straat et al. and Zaanen et al. [17, 18]. While this RTW definition is needed to compare the results with the prospective studies, it also means that comparisons with other studies (vice versa) should be performed carefully.

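### The primary effectiveness outcome is set as first RTW and/or full RTW under one 0.05 level, so the protocol does not say whether one endpoint is enough or both must succeed

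*Protocol article*

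**What the plan says.** - **Outcome.** Under Primary outcomes, the effectiveness study has two endpoints joined by *and/or*: "the primary outcomes are first day of RTW and/or first day of full RTW". The Effectiveness part of Statistical methods uses *and/or* for the same two endpoints again.
- **Comparator by endpoint.** The same Primary outcomes section gives each endpoint its own external cohort: "For the first days to RTW the prospective Expect to Work study" and "for full RTW the ACTIVE trial comparison group".
- **Comparator in the analysis section.** The Effectiveness section does not repeat that pairing: "Hazard ratios including 95% confidence intervals will be calculated for the intervention group and tested against both control groups". Study design names both cohorts together, also without a split by endpoint: "care as usual, namely the Expect to Work cohort and the ACTIVE trial".
- **Error rate and sizing.** Sample size gives a single calculation, "with a power of 0.8 and a significance level of 0.05". Sidedness is not stated. On the effect: "The effect size was calculated with a mean difference of two weeks in comparison to a Dutch study on RTW after KA". The Discussion describes the cited study (reference 15) as asking patients "what the duration from operation until the first day of RTW was", so the sizing refers to first RTW.
- **Relevance thresholds.** The Effectiveness section and the Discussion set two weeks for first RTW and one week for full RTW.

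**The concern.** *And/or* permits two different decision rules. If both endpoints must succeed, no adjustment of 0.05 is needed. If either is enough, the overall chance of a false claim rises above the level stated for one test. The article gives the single level and the single sample size without saying which rule applies.

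The endpoints also have different external control cohorts, so they may disagree for reasons unrelated to the pathway. Nothing says which would then answer the first aim.

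The setting makes an open choice costly. The comparison is not randomised, the lead author acts as a medical case manager, and the case managers collect the RTW data. Registration was retrospective.

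**Working it through.** **Inputs.** Level 0.05 and power 0.80 (Sample size). Two endpoints, each with one cohort (Primary outcomes), give k = 2 tests. Each endpoint against each cohort, the literal reading of the Effectiveness sentence, gives k = 4. The documents give no correlation between the test statistics, so 0 to 0.7 is assumed and 0.9 is added as an extreme.

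**Stated figure.** The minimum of 125 cannot be reproduced, because no standard deviation, allocation ratio or test is given. It is not needed for the error rates below.

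**Step 1: which event to count.** A two-sided test at 0.05 gives a false result favouring BAAS with probability 0.025. The relevant benchmark for a false claim of effectiveness is therefore 2.5%, unless the 0.05 is one-sided.

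**Step 2: independent tests.** Chance of at least one = 1 − (1 − a)^k.
- Favouring BAAS, a = 0.025: k = 2 gives 1 − 0.975² = 0.0494; k = 4 gives 1 − 0.975⁴ = 0.0963.
- Either direction, or one-sided 0.05, a = 0.05: k = 2 gives 1 − 0.95² = 0.0975; k = 4 gives 1 − 0.95⁴ = 0.1855.

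**Step 3: correlated tests.** Equicorrelated normal test statistics with correlation ρ, each tested two-sided at 0.05:

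| ρ | k = 2, favouring BAAS | k = 4, favouring BAAS | k = 2, either direction | k = 4, either direction |
|---|---|---|---|---|
| 0 | 4.9% | 9.6% | 9.75% | 18.5% |
| 0.5 | 4.5% | 7.8% | 9.1% | 15.6% |
| 0.7 | 4.2% | 6.5% | 8.4% | 13.0% |
| 0.9 | 3.5% | 4.7% | 7.0% | 9.4% |
| Nominal, one test | 2.5% | 2.5% | 5% | 5% |

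If the 0.05 is one-sided, two tests give 9.75% at ρ = 0 and 8.0% at ρ = 0.7, against 5%.

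**Step 4: cost of keeping either-suffices with a Bonferroni split.** Required N = 125 × [(z(1−a/2) + z(0.80)) / (z(0.975) + z(0.80))]², which does not depend on the missing standard deviation.
- a = 0.025 (two tests): 125 × 1.211 = 151.4, so 152 evaluable. With 125 evaluable, power falls from 0.80 to 0.71.
- a = 0.0125 (four tests): 125 × 1.421 = 177.6, so 178 evaluable. With 125 evaluable, power is 0.62.

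A fixed test order needs neither change: the first test keeps 0.05 and N = 125.

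**The case against.** **No success rule is stated.** The article never says that one endpoint is enough. *And/or* may be loose wording for two outcomes, each with its own definition, cohort and relevance threshold, to be reported side by side. That is fair: either-suffices is what the wording permits, not what it announces. The open definition of the primary outcome remains.

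**Hierarchy and multiplicity may sit in an unseen document.** An analysis plan could hold a multiplicity method, and its absence from an article is no finding. But the definition of the primary outcome is in this text and is left open here.

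**The comparator statements may agree.** Two hazard ratios, each tested against its own cohort, are together tested against both control groups. This is the natural reading, so two tests is the main count. A reader might infer a flat contradiction and a fixed set of four tests. The text does not support that; four is only a literal possibility.

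**The error rate is easily overstated.** A reader might infer that an ineffective pathway has well over a 5% chance of being called effective, quoting 8.4% to 18.5%. Those figures count significant harm as well as benefit. For two two-sided tests, the chance of a false result favouring BAAS stays just under 5%; the proper benchmark is 2.5%.

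**Ranking the endpoints is a choice.** Full RTW is a stop criterion of the pathway, and its ACTIVE cohort is the economic comparator. The sizing rests on a third study, so it points to first RTW as the endpoint but does not itself select Expect to Work. The comparator comes from the Primary outcomes pairing.

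**Conclusion.** The point holds as a defect in how the primary outcome is fixed. The wording leaves open whether one or both endpoints must succeed, while one 0.05 level and one calculation, tied to first RTW, are stated. If either suffices:

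- With the stated pairing (two tests), the chance of a false result favouring BAAS is 1.7 to 2 times nominal: 4.2% to 4.9% against 2.5%.
- On the literal four-test reading, it is 2.6 to 3.9 times nominal: 6.5% to 9.6% against 2.5%.

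These ranges rest on two-sided tests and an assumed correlation of 0.7 down to 0. The tests share the same BAAS patients and related outcomes, so the independent-test values are upper ends. At a correlation of 0.9 the inflation is smaller (3.5% and 4.7%) but still present. The calculation covers multiplicity only and says nothing about confounding between cohorts.

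**What to change.** 1. In Primary outcomes, replace *and/or* with a fixed test order at 0.05. Test first day of RTW against Expect to Work first, because the two-week difference used for sizing refers to a first-RTW study and equals the relevance threshold for that endpoint. Test full RTW against the ACTIVE usual-care group second, as confirmatory only if the first is significant.
2. State whether 0.05 is one- or two-sided.
3. Reword the hazard ratio sentence in the Effectiveness section so that each endpoint is tested against its own cohort, and label any cross-cohort comparison as sensitivity analysis. Remove the second *and/or* there.
4. Record this as a dated amendment that says what outcome data had been seen. The inclusion window opened in January 2022 and registration followed in January 2023, so this is a change to a study under way.

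Cost: an amendment, with no change to the 0.05 level or to N. Full RTW could not support the main claim alone if first RTW is not significant; it would then be reported with its estimate and interval as exploratory. If the sponsor wants either endpoint to be able to carry the claim, the alternative is the split level, at 152 evaluable patients for two tests or power of about 0.71 with 125.
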